### Eligibility criteria {10}

#### Inclusion criteria

In order to be eligible to participate in this study, a patient must meet all of the following criteria: (1) provide written informed consent prior to initiation of any study procedures; (2) understand and agree to comply with planned study procedures; (3) agree to the collection of oropharyngeal swabs and venous blood per protocol; (4) be male or non-pregnant female adult ≥18 years of age at the time of enrolment; and (5) have laboratory-confirmed SARS-CoV-2 infection as determined by RT-PCR in any specimen no more than 72 h prior to randomization. Both asymptomatic and symptomatic cases (mild/moderate/severe) are eligible for enrolment.

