## Outcomes {12}

COVID-19 is a new disease and our understanding of it is evolving. To align this study with other international studies, the objectives, endpoints and some other aspects of the WHO’s Master Protocol [42] have been adopted as appropriate with modifications to suite the Lagos context. There are three objectives—one primary and two secondary objectives. Each objective has three sub-objectives—one for comparing chloroquine phosphate added on to standard therapy and standard therapy alone; one for comparing hydroxychloroquine sulphate added on to standard therapy and standard therapy alone; and one for comparing lopinavir/ritonavir added on to standard therapy and standard therapy alone.

A special WHO committee developed the ordinal scale that will be used in this study for the primary endpoint [43]. This study uses a combined endpoint (based on the WHO 7-point ordinal scale) of both “clinical status and mortality” at day 15. Hence, superiority can be demonstrated when either arm shows a significant effect on the variables for clinical status OR mortality by day 15. This endpoint is particularly useful in our population given the low mortality rate, and a combined endpoint would increase the study power. The secondary endpoints will enable evaluation of the effect of the trial medications on the rate of change in the clinical condition of COVID-19 patients, as well as the safety of the trial medications (Table 3).

**Table 3 Tab3:** LACTT objectives and endpoints

**Primary objectives**	**Primary endpoints**

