1. To evaluate the clinical efficacy of chloroquine phosphate, hydroxychloroquine sulphate and lopinavir/ritonavir added on to standard therapy relative to standard therapy alone for treatment of individuals with laboratory-confirmed COVID-19 1.1 To evaluate the clinical efficacy of chloroquine phosphate added on to standard therapy relative to standard therapy alone for treatment of individuals with laboratory-confirmed COVID-19 1.2 To evaluate the clinical efficacy of hydroxychloroquine sulphate added on to standard therapy relative to standard therapy alone for treatment of individuals with laboratory-confirmed COVID-19 1.3 To evaluate the clinical efficacy of lopinavir/ritonavir added on to standard therapy relative to standard therapy alone for treatment of individuals with laboratory-confirmed COVID-19	*Seven-point ordinal scale assessed on day 15* 1. Not hospitalized, no limitations on activities 2. Not hospitalized, limitation on activities 3. Hospitalized, not requiring supplemental oxygen 4. Hospitalized, requiring supplemental oxygen 5. Hospitalized, on non-invasive ventilation or high flow oxygen devices 6. Hospitalized, on invasive mechanical ventilation 7. Death
**Secondary objectives**	**Secondary endpoints**
1. To evaluate the effect of chloroquine phosphate, hydroxychloroquine sulphate and lopinavir/ritonavir added on to standard therapy compared to standard therapy on the rate of progression/resolution of COVID-19 1.1 To evaluate the effect of chloroquine phosphate added on to standard therapy compared to standard therapy on the rate of progression/resolution of COVID-19 1.2 To evaluate the effect of hydroxychloroquine sulphate added on to standard therapy compared to standard therapy on the rate of progression/resolution of COVID-19 1.3 To evaluate the effect of lopinavir/ritonavir added on to standard therapy compared to standard therapy on the rate of progression/resolution of COVID-19	1. Clinical status on the 7-point ordinal scale on days 3, 5, 8, 11 and 29 2. National Early Warning Score assessed daily while hospitalized and on day 15 3. Duration of supplemental oxygen 4. Duration of mechanical ventilation 5. Duration of hospitalization or isolation 6. SARS-CoV-2 clearance time based on samples taken on days 3, 5, 8, 11, 15 and 29

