## Assignment of interventions: allocation

### Sequence generation {16a}

Prior to study initiation, a randomization list will be generated (using the statistical programming language R, version 3.6.3 to enable random assignment to each of the trial arms at each of the study sites using an equal allocation ratio (for instance 1:1:1:1 for four arms)). If arms are added to or dropped from the trial, randomization will proceed with an equal probability of assignment to each of the remaining arms.

Randomization will be stratified by site and at each site by severity of illness at enrollment yielding two strata: (1) asymptomatic (no clinical symptoms or signs) and (2) symptomatic (presence of clinical symptoms and/ or signs). The R code used to generate the randomization lists will store the seed so that the generated lists are reproducible.

The randomization list will be generated using permuted block randomization with two block sizes, with the larger block size chosen so that it is not a multiple of the smaller block. Using permuted block randomization rather than simple randomization will avoid the possibility of long periods of time during which participants are not allocated to one or more arms of the study—a scenario which could introduce bias to the study due to time effects. Two block sizes would make it more difficult for clinicians (who will be unaware of the block sizes) to guess any part of the allocation sequence, thus, reducing the potential for the introduction of selection bias by well-meaning staff members at study sites.

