#### Statistical methods for analyzing secondary outcomes

The following analyses will be performed for the comparison of each experimental arm to the placebo arm when full enrolment has been achieved. For these analyses, the alpha level used is that of the analysis for the primary outcome when full enrolment has been achieved.
The Mantel-Haenszel odds ratio estimator and test statistic will be applied to the strata defined by clinical signs and symptoms (asymptomatic versus symptomatic).Differences in time-to-event endpoints (e.g. time to negative SARS-CoV-2 status) by treatment will be summarized with Kaplan-Meier curves and 95% confidence bounds.Change in ordinal scale at specific time points will be summarized by proportions (e.g. proportion who have a 1-, 2-, 3- or 4-point improvement or worsening).Duration of event (e.g. duration of mechanical ventilation) will be summarized according to median days with quartiles.Incidence data (e.g. incidence of new oxygen use) will be summarized as a percent with 95% confidence intervals.Categorical data (e.g. 28-day mortality or ordinal scale by day) will be summarized according to proportions with confidence intervals on the difference or odds ratios for a binary or multiple category scale, respectively.Logistic regression analyses will be undertaken to assess the effect of covariates on outcomes.

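### Durations of oxygen and ventilation are compared by median and quartiles in an all-severity population with no stated value for never-users, so the summary may be largely zeros or may compare groups selected after randomization

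*Protocol article*

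**What the plan says.** Table 3 (Outcomes {12}) lists six endpoints for the secondary objective on rate of progression or resolution. Two of them are "3. Duration of supplemental oxygen 4. Duration of mechanical ventilation".

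Statistical methods for analyzing secondary outcomes sets the statistic: "Duration of event (e.g. duration of mechanical ventilation) will be summarized according to median days with quartiles". The sentence that opens the list gives its purpose: "The following analyses will be performed for the comparison of each experimental arm to the placebo arm when full enrolment has been achieved". The next sentence carries over the alpha level of the final primary analysis. The same list includes a separate line: "Incidence data (e.g. incidence of new oxygen use) will be summarized as a percent with 95% confidence intervals".

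On the population, Inclusion criteria states: "Both asymptomatic and symptomatic cases (mild/moderate/severe) are eligible for enrolment". No minimum share of severe cases is set. Sequence generation {16a} stratifies by site and by asymptomatic versus symptomatic, not by oxygen or ventilation need at baseline. Section {20c} makes the analysis population intention-to-treat.

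Nothing in the article says whether a participant who never receives oxygen or ventilation counts as 0 days or is left out. A worst-rank rule for deaths is given only for time to meeting discharge criteria.

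**The concern.** A duration of support is naturally defined only for those who receive it. In a trial that enrols from asymptomatic to severe, many participants may never do so. The chosen statistic then works poorly under either obvious convention.

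- If never-users count as 0, the median and possibly both quartiles are 0 in every arm, and the summary cannot distinguish the arms.
- If never-users are dropped, the arms are compared among participants who went on to need support. A drug can change who belongs to that group, so it is no longer protected by randomization. A drug that prevents short courses leaves the longer ones behind and can appear to lengthen support.

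At stake is whether these two of the six endpoints can inform the objective they serve. The problem arises even if nobody dies.

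**Working it through.** The protocol gives no figure for these durations and no rate of oxygen or ventilation use, so there is nothing to reproduce. The check runs over assumed user shares.

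**Inputs.** 200 per arm (Sample size {14}); share p of an arm that ever uses the support (assumed, 2% to 60%).

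**Step 1: never-users entered as 0.** With n = 200, the median is 0 if there are fewer than 100 users, and the upper quartile is 0 if there are fewer than 50. With the number of users X ~ Binomial(200, p):

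- P(median = 0) = P(X ≤ 99)
- P(upper quartile = 0) = P(X ≤ 49)

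| Share p | Expected users (200 × p) | P(median = 0) | P(upper quartile = 0) |
|---|---|---|---|
| 2% | 4 | 1.000 | 1.000 |
| 5% | 10 | 1.000 | 1.000 |
| 10% | 20 | 1.000 | 1.000 |
| 20% | 40 | 1.000 | 0.951 |
| 24% | 48 | 1.000 | 0.603 |
| 30% | 60 | 1.000 | 0.051 |
| 40% | 80 | 0.997 | 0.000 |
| 45% | 90 | 0.911 | 0.000 |
| 50% | 100 | 0.472 | 0.000 |
| 60% | 120 | 0.002 | 0.000 |

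If all four arms share the same p, the median is 0 in all of them with probability P(X ≤ 99)^4: above 0.9999 at 30%, 0.989 at 40% and 0.690 at 45%. With 180 per arm (200 less 10% loss) the picture is the same: at 20%, P(upper quartile = 0) is 0.941; at 40%, P(median = 0) is 0.996.

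**Step 2: where this trial is likely to lie.** This is inference. Outcomes {12} says of the primary endpoint: "This endpoint is particularly useful in our population given the low mortality rate, and a combined endpoint would increase the study power". The background reports 603 deaths in 26,484 Nigerian cases, and 603 / 26,484 = 2.3%. Together with eligibility of asymptomatic cases, this makes ventilation in a quarter or more of an arm hard to credit. For oxygen the documents fix no such limit, and severe cases are eligible.

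**Step 3: users only.** The comparison rests on the expected users in the table: 4 to 10 per arm at shares of 2% to 5%, and 20 to 40 at 10% to 20%.

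To illustrate selection, assume that 20% of controls need support, with duration rising with latent severity, and that treatment prevents the mildest quarter of courses and changes no other.

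| | Control | Treatment |
|---|---|---|
| Share ever on support | 20% | 15% |
| Quartiles, all participants (days) | 0 / 0 / 0 | 0 / 0 / 0 |
| Median, users only (days) | 5.5 | 6.8 |
| Mean, all participants (days) | 1.29 | 1.15 |

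The all-participant quartiles miss the benefit, and the users-only median reverses it.

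**The case against.** Four points can be made for the plan.

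- **Coding rules for never-users may sit in the SAP, which is not shown.** This stands as far as coding goes, and the missing rule alone would be no finding. But the statistic is chosen in this text, and it serves neither coding well when use is low.
- **The durations are only summarized.** The line names no test, which is true. The opening of the list nevertheless presents the summaries as arm-versus-placebo comparisons.
- **Prevention is covered elsewhere.** This largely stands. Suppose 24% versus 12% ever start oxygen, with 200 per arm. The incidence line shows a difference of 12 points with standard error √(0.24 × 0.76/200 + 0.12 × 0.88/200) = 0.038, so a 95% interval of about 5 to 19 points. Points 4 to 6 of the ordinal scale, scored on several days, also register support. These lines do not measure how long support lasts, and the incidence line concerns new use only.
- **Participants already on support at baseline form a group fixed before randomization, in which duration can be compared validly.** This is correct, but the article neither plans that subgroup nor stratifies by baseline support.

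A reader might infer that the medians and quartiles must be 0 in every arm whatever the drugs do, or that the trial cannot show prevention of respiratory support. The documents support neither. No support rate is given; at oxygen use between 25% and 50% the upper quartile can carry information, and above 50% the median can. Prevention has its own planned summaries.

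**Conclusion.** The point holds as a poorly chosen statistic for two secondary endpoints, conditional on how often support is used. With never-users as 0, ventilation duration is very likely to be summarized as 0 / 0 / 0 in every arm. The median for oxygen duration would almost surely be 0 in every arm at user shares up to about 40%, and its upper quartile would usually be 0 only at about 20% or below. With users only, the comparison is small and selected after randomization, and a benefit can look like harm. The user shares and the illustration are assumptions. The primary endpoint is unaffected, and the loss is partly offset by the incidence and ordinal-scale summaries. This is a low-severity improvement that is cheap to make.

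**What to change.** Define both endpoints for every randomized participant, for example as days alive and free of supplemental oxygen, and days alive and free of mechanical ventilation, to a fixed horizon.

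- **Horizon.** Use one that the data support. Table 4 schedules clinical assessment to day 15, so day 15 is the simple choice. Day 29 is possible by combining the daily records kept while a participant is hospitalized or isolated with the day-29 treatment review.
- **Deaths.** Give deaths the worst value, in line with the rule already set for time to meeting discharge criteria. Simply counting days on support with never-users as 0 would not do, because an early death would then score as a short course.
- **Comparison.** Use a rank or ordinal test stratified by the randomization strata (site and symptomatic status), with a matching effect estimate. A median of support-free days would sit at its ceiling for the same reason that the median duration sits at 0.
- **Users-only figures.** Keep the median and quartiles among users as description, without an arm comparison, beside the planned incidence of new oxygen use.

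The cost is analysis-plan wording and a small amount of extra analysis, with no added participants or visits. The composite is slightly less direct to interpret than a duration.

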#### Comparing time to meeting criteria for successful discharge from the COVID-19 treatment centre between participants receiving investigational therapeutics, relative to the control arm

Differences in median days to becoming eligible for discharge will be tested using the Wilcoxon rank-sum test, imputing deaths prior to day 28 as the worst rank, with earlier deaths having a worse rank than later deaths.Discharge decisions may not always be based on objective clinical data. For these reasons, time to meeting criteria for successful discharge will be analysed rather than time to actual discharge.We will tabulate the sample size, number (%) who became eligible for discharge within 29 days, mean, median and standard deviation of days to discharge eligibility among those for whom the endpoint is available. *P*-values for test of medians using Wilcoxon rank-sum test.Side-by-side plots and boxplots of time to meeting criteria for successful discharge by arm, separately for symptomatic and asymptomatic cases, will be prepared.

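### Durations of oxygen, ventilation and hospital stay are compared as plain medians with no rule for deaths, and the discharge analysis handles deaths inconsistently

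*Protocol article*

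**What the plan says.** The article's Table 3 (Outcomes {12}) lists, under the objective on rate of progression or resolution, "3. Duration of supplemental oxygen 4. Duration of mechanical ventilation 5. Duration of hospitalization or isolation". The section on statistical methods for secondary outcomes states how they are handled: "Duration of event (e.g. duration of mechanical ventilation) will be summarized according to median days with quartiles". That line belongs to a list introduced by "The following analyses will be performed for the comparison of each experimental arm to the placebo arm when full enrolment has been achieved", so the medians are meant for comparing arms. Nothing is said about participants who die, or about whether the denominator is users of the support, survivors or all randomised participants.

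The section on time to meeting discharge criteria does have a death rule. It uses the Wilcoxon rank-sum test, "imputing deaths prior to day 28 as the worst rank, with earlier deaths having a worse rank than later deaths", and states that "time to meeting criteria for successful discharge will be analysed rather than time to actual discharge". The table planned for that endpoint gives the number and percentage eligible within 29 days and the "mean, median and standard deviation of days to discharge eligibility among those for whom the endpoint is available", with the rank-sum p-value described as a test of medians.

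**The concern.** Death ends oxygen, ventilation and hospital stay. If the duration is taken as days until the support stops for whatever reason, a participant who dies on day 4 has a short duration, and a short duration reads as a good result. Ventilated participants are the ones most likely to die, so that median is the most exposed. The authors recognised the problem for discharge eligibility and did not extend the remedy to the three related durations.

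The discharge section has two faults of its own:

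- The worst-rank rule stops short of day 28, while the table and the last visit run to day 29. Deaths at the end of follow-up have no assigned rank.
- The median shown leaves out those who die before becoming eligible, while the p-value beside it counts them as worst. The two describe different populations and can disagree in direction.

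**Working it through.** The article gives no figure for the duration endpoints, so there is none to reproduce. The check is whether a plain median moves the wrong way when mortality rises, and by how much.

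**Inputs.** From the article: follow-up to day 29; mortality described only qualitatively ("This endpoint is particularly useful in our population given the low mortality rate"); national deaths over cases in the Background, 603/26,484 = 2.3%, used as the low end of the range; asymptomatic and mild cases eligible. All other inputs are assumptions:

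- Oxygen or ventilation users: median duration 10 days in survivors, median 4 days to death.
- Hospital stay, all participants: median 12 days in survivors, median 5 days to death.
- Lognormal times, log-scale SD 0.5 for durations and 0.6 for time to death.

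**Formulas.** Let m be mortality, S(x) the distribution function of duration without death and T(x) that of time to death.

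- Plain median, clock stopped at death: solve (1 − m)·S(x) + m·[1 − (1 − S(x))(1 − T(x))] = 0.5.
- Deaths ranked worst: solve (1 − m)·S(x) = 0.5; not reached once m is 0.5 or more.

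**Users of oxygen or ventilation**

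| Mortality among users | Plain median (days) | Deaths ranked worst (days) |
|---|---|---|
| 20% | 8.7 | 11.7 |
| 30% | 7.9 | 13.3 |
| 40% | 7.1 | about 16 |
| 50% | 6.3 | not reached |

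From 20% to 40% mortality the plain median shortens by 8.7 − 7.1 = 1.6 days, an apparent benefit, while the death-ranked median lengthens. The survivors-only median stays at 10.0 days throughout, so it does not register the deaths at all.

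**A different distribution.** With gamma durations (shape 2, same medians of 10 and 4 days), treating the two groups as a simple mixture, the plain median is 7.5, 6.1 and 5.0 days at 30%, 50% and 70% mortality. With death set to day 29 it is 14.9, 29 and 29. The direction does not depend on the distribution chosen.

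**Hospital stay.** From 2.3% to 10% mortality the plain median falls from 11.84 to 11.27 days, about 0.6 day. With deaths ranked worst it rises from 12.2 to 12.9 days.

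**The other denominator.** If every randomised participant counts and those never ventilated score 0, the ventilation median is 0 in every arm whenever fewer than half are ventilated. All three quartiles are 0 when fewer than a quarter are. The summary then shows neither benefit nor harm.

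**Day 28 against day 29.** Randomisation is on day 1 in the schedule of assessments. If day 28 is a study day, deaths on days 28 and 29 have no rank. If it means 28 days after randomisation, that is study day 29, and deaths on that last day have none. Either way the rule stops short of the table's limit.

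**The case against.** The strongest reply is that the article does not say a death counts as a short duration. Death handling and the population for a descriptive summary are often left to the analysis plan, which is not shown. That stands as a limit on the wording: the distortion belongs to the default reading of a plain median and is not a stated rule. It does not remove the point, because the article does fix the summary statistic and its use for comparing arms. Each common denominator leaves a difficulty: users only is truncated by death and selected after randomisation, survivors only ignores deaths, and all randomised may give 0 everywhere.

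Other parts of the reply also stand:

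- A reader might infer that a drug that raises mortality would come out as beneficial overall, or that the whole progression/resolution objective could be answered in the wrong direction. The document does not support this. Death is the worst category of the primary scale at day 15 and of the first-listed secondary endpoint on days 3, 5, 8, 11 and 29, and 28-day mortality is among the categorical outcomes to be summarised. The durations are three of six endpoints under that objective, with no test named for them.
- Hospital stay is partly covered by the worst-rank discharge analysis, although the listed hospitalisation or isolation endpoint is not expressly tied to it.
- Mortality of 20% to 70% among users is assumed, and few participants may be ventilated. Under the gamma model at 50% against 70% mortality, 10 ventilated participants per arm give a mean difference in medians of 1.2 days with SD 2.8, and 20 per arm give 1.1 with SD 2.0. A one-day gap would be within noise.
- The day 28 mismatch is partly a matter of labelling and would affect at most a death or two. The discharge table also prints the number eligible, so its conditional median can be recognised for what it is.

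**Conclusion.** The point holds for the oxygen and ventilation durations. If the clock stops at death, more deaths among users give a shorter plain median: about 1.6 days shorter between 20% and 40% mortality under the assumed durations, where a death-ranked median moves the other way. The direction follows from the construction and agrees under both distributions; the size rests on assumed mortality and durations. For hospital stay the effect is small at low mortality. The primary and mortality results are not reversed. If all randomised participants form the denominator, the ventilation median is likely to be uninformative rather than misleading.

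The two faults in the discharge section stand on the text alone: a death rule that ends before follow-up does, and a displayed median computed on a different population from the p-value next to it. A better method is already in the document and needs little to extend, so the change is worth making.

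**What to change.** 1. For the between-arm comparison, replace the three plain durations with days alive and free of oxygen, of ventilation and of hospital or isolation to day 29, in all randomised participants. Give death by day 29 the worst value, below that of a survivor with no free days, and compare arms with the rank-sum test already named for discharge eligibility.
2. Show the number of deaths beside each comparison. Keep raw durations among users or survivors as description only, with the denominator stated.
3. In the discharge section, extend the worst-rank rule to deaths through day 29, say how days are counted, and tabulate the median on the same death-ranked data as the p-value.

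The cost is a few sentences and a little reprogramming. The measure uses the start and stop dates that the planned durations already need, plus the date of death. It adds rank tests where only summaries were planned, so they should be labelled secondary. If few participants are ventilated, ventilation-free days may have the same median in every arm; the full distribution should therefore be shown as well.
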